#### Withdrawal and termination criteria

2.3.3

Withdrawal criteria: (1) Individuals unable to complete the entire treatment and observation process; (2) Individuals who cannot fully understand the various forms and questionnaires provided during the study and require assistance; (3) Individuals concurrently receiving other treatments; (4) Individuals with poor compliance; (5) Individuals with incomplete data affecting efficacy and safety evaluation; (6) Individuals experiencing severe adverse reactions or complications who are unsuitable for continued treatment and are therefore withdrawn from the trial; and (7) Individuals who have not completed more than 2/3 of the treatment course (including those withdrawn from the trial and lost to follow-up).

Termination criteria: Participants experiencing severe adverse events or reactions making it inappropriate to continue in the study; major errors found in the study design or significant deviations from the facts; participants who develop serious complications or deteriorate in a condition requiring emergency measures; participants withdrawing from the clinical study; patients who are uncooperative or noncompliant with treatment, despite repeated explanations from clinicians; during the trial, researchers should retain all original trial records and document in detail the reasons and timing for withdrawal. Those who have completed more than half of the treatment regimen should be included in the efficacy statistics.

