### Interventions

2.6

Participants in both groups of this study will be assessed on the first-day post-surgery, with treatment beginning on the second day and continuing for three consecutive days, totaling three sessions, with needles retained for 30 min each time. Subsequently, the treatments will be conducted three times a week for 4 weeks. Both treatments will be administered by trained acupuncturists who hold a valid practitioner certificate and have over 5 years of clinical experience, having undergone standardized training before the trial to ensure consistency. After discharge, patients need to undergo acupuncture treatment in the outpatient department; if numbness symptoms disappear, acupuncture treatment should be halted, and follow-up will continue per the experimental protocol.

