### Western medicine treatment for all included patients

2.7

All patients included in this study received basic conventional Western medicine treatment: starting from the second day after surgery, they were administered anti-inflammatory and analgesic treatment (celecoxib capsules 200 mg, 1 capsule/time, 2 times/day) combined with neurotrophic treatment (mecobalamin tablets 0.5 mg, 1 tablet/time, 3 times/day) for 28 days (Note: Patients were required to continue treatment at the outpatient clinic after discharge. If their numbness symptoms disappeared, the basic Western medicine treatment was discontinued, which was recorded in the experimental protocol, and follow-up was continued according to the experimental protocol).

Drug Sources:

Mecobalamin Tablets: Produced by Jiangxi Qingfeng Pharmaceutical Co., Ltd., Approval Number: Guoyao Zhunzi H20051440.Celecoxib Capsules: Produced by Pfizer Pharmaceutical Co., Ltd., Approval Number: Guoyao Zhunzi J20120063.

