General information	√				
Numbness VAS score	√	√	√	√	√
Nylon rope test	√	√	√		
Needle punching test	√	√	√		
JOA score	√	√	√	√	√
Lower Limb EMG	√	√	√		
Chinese medicine evidence score	√	√	√	√	√
SF-36 (Quality of Life Scale)	√	√	√	√	√
VAS score	√	√	√	√	√
Safety observations		√	√	√	√

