### Safety assessment

2.9

During the study, observations and records will be made of any potential adverse reactions, such as bleeding caused by acupuncture, hematoma, needle sickness, pain at the acupuncture site, infection, as well as skin rupture and infection after moxibustion. The primary records will include the incidence rate of adverse events and the grading of safety evaluations. Adverse events will be graded according to the Common Terminology Criteria for Adverse Events (CTCAE) Version 5.0. Mild (Grade 1): asymptomatic or mild symptoms, requiring no intervention; Moderate (Grade 2): symptoms are evident and require non-invasive treatment (such as local hemostasis, disinfection, etc.); Severe (Grade 3 and above): symptoms are severe, requiring hospitalization or leading to discontinuation of treatment. The evaluation time points are detailed in Table 1.

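### Stopping treatment for a severe adverse reaction also takes the patient out of the trial, and the article provides for none of that patient's remaining scheduled observations

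*Protocol article*

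**What the plan says.** Section 2.3.3 of the protocol article lists, as withdrawal criterion (6), "Individuals experiencing severe adverse reactions or complications who are unsuitable for continued treatment and are therefore withdrawn from the trial". The first termination criterion in the same section is "Participants experiencing severe adverse events or reactions making it inappropriate to continue in the study". For patients who leave, the section asks only that "researchers should retain all original trial records and document in detail the reasons and timing for withdrawal".

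Section 2.9 places adverse event recording within trial participation: "During the study, observations and records will be made of any potential adverse reactions". The Table 1 row "Safety observations" is ticked at 1 week and 4 weeks and at 12 and 24 weeks after treatment.

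Stopping because of a good result is handled differently. Section 2.6 says that "if numbness symptoms disappear, acupuncture treatment should be halted, and follow-up will continue per the experimental protocol". Section 2.7 says of patients whose basic medication was stopped for the same reason that "follow-up was continued according to the experimental protocol".

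Section 2.12 commits all analyses to the intention-to-treat principle with every randomized participant included.

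**The concern.** Stopping the assigned treatment and leaving the trial are separate events. Criterion (6) joins them: unsuitability for further treatment is given as the reason for withdrawal from the trial. Followed as written, it removes a patient from the remaining visits because of harm, whereas a patient who stops because of recovery stays in.

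Evaluating safety is a stated objective. For patients withdrawn under this rule, three things would be missing: how the event resolved, whether anything else happened later, and the remaining efficacy measurements. Because the loss depends on harm, it need not be equal between arms. Section 2.9 lists skin rupture and infection after moxibustion, which is given only in the intervention group, while electrical stimulation is given only in the control group.

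**Working it through.** No figure in the article bears on this point, so the check is a comparison of sections followed by a count of visits.

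**Comparison of the rules**

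- Treatment stops because numbness has resolved (sections 2.6 and 2.7): follow-up continues, stated explicitly for both acupuncture and medication.
- Treatment stops because of a severe reaction (section 2.3.3, criterion 6): the patient is withdrawn from the trial. The termination criterion likewise concerns continuing in the study, not continuing treatment.
- After withdrawal (section 2.3.3): existing records are kept, and the reason and time are documented. No further visit or contact is mentioned.
- After unblinding for a serious adverse event (section 2.4): the patient may withdraw from the trial. Continued observation is again not mentioned.
- Severe grade (section 2.9): Grade 3 and above, which includes events that lead to treatment being discontinued. The events graded most serious are therefore among those that can trigger removal.

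The authors do separate the two decisions in sections 2.6 and 2.7, so the different wording in section 2.3.3 cannot be put down to the article never drawing the distinction.

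**Count of observations lost per patient**

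Table 1 has four safety observations: 1 week, 4 weeks, and 12 and 24 weeks after treatment. If no observation follows withdrawal:

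- withdrawn before the 1-week visit: 4 − 0 = 4 lost;
- withdrawn between the 1-week and 4-week visits: 4 − 1 = 3 lost;
- withdrawn at the end of treatment, after the 4-week visit: 4 − 2 = 2 lost.

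The numbness VAS, the primary outcome, has the same four post-baseline times, so the same counts apply to it. JOA, TCM syndrome score, SF-36 and the other VAS also share them. The monofilament, pinprick and electromyography assessments end at 4 weeks, so they lose at most two.

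**Effect on the planned analyses**

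- Incidence and grade (sections 2.9 and 2.12): the triggering event was observed before withdrawal and enters these tables. Events after withdrawal would not.
- Primary mixed model (section 2.12): a withdrawn patient stays in the intention-to-treat set, but the missing scores would be filled by multiple imputation or, in the sensitivity analysis, by carrying the last value forward. Imputed values would replace measurements that already scheduled visits could have supplied.

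**Number of patients**

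The article gives no expected rate of severe reactions, so the number affected cannot be calculated.

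**The case against.** The strongest reply is that no sentence says observation ends at withdrawal. The document is a journal article, and following an adverse event to its outcome is a detail that a fuller protocol may contain. The section 2.3.3 list also reads partly as a classification of cases: it includes patients with incomplete data, and it ends with who counts in the efficacy statistics. This stands to the extent that the loss is the consequence of the wording and not a stated instruction. It does not remove the point, because the article does more than stay silent: it makes leaving the trial follow from stopping treatment, and it states the opposite arrangement for patients who improve.

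The second reply is that the safety results the article plans to report, incidence and grade, still include the triggering event. That stands in full.

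Stronger readings are tempting but not supported:

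- A reader might infer that everyone who is harmed is lost. Both clauses are conditional and cover only severe events judged to preclude continuing. Nor is harm the only ground for withdrawal: poor compliance and incomplete treatment are others.
- A reader might infer that unresolved severe events at 24 weeks will be nearly absent by design, or that late harm will be understated. The article does not plan to report the first quantity. It gives no rate from which to size the second, and the reactions it lists are mostly local and related to the procedure.
- A reader might infer that criterion (3), on concurrent other treatments, also catches patients treated for a Grade 2 event, defined as "Moderate (Grade 2): symptoms are evident and require non-invasive treatment". The examples given there are local hemostasis and disinfection, which are hardly other treatments in that sense. Section 2.12 treats prohibited medication as a per-protocol exclusion, which leaves those patients in the intention-to-treat analysis.

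**Conclusion.** The point holds in limited form. As worded, section 2.3.3 turns stopping treatment for a severe adverse reaction into leaving the trial, which does not fit with the safety schedule in Table 1, with sections 2.6 and 2.7, or with an intention-to-treat analysis that needs outcome data from all randomized patients. The triggering event remains counted. Its later course, later events and the remaining outcomes would be lost.

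For each such patient the loss is two to four of four safety observations, and as many numbness scores. The total is unknown, and any imbalance between arms is possible but not demonstrated. The conclusion assumes that withdrawal is applied as written and that no document outside the article provides for continued observation. It concerns data collection and makes no judgement on when treatment ought to stop. It is worth correcting, though nothing here shows that the primary comparison is invalid.

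**What to change.** Reconcile section 2.3.3 with sections 2.6, 2.7, 2.9 and 2.12 and with Table 1 by separating two decisions: stopping assigned treatment and leaving the trial. Reword criterion (6) and the first termination criterion so that a patient whose treatment is stopped for an adverse event remains in all later Table 1 safety and outcome observations unless consent is withdrawn. If a fuller protocol already says this, bring the article's wording into line with it. The grounds for stopping treatment stay as the protocol has them.

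The cost is a wording amendment through the route in section 2.1, plus keeping any affected patients in visits that are already scheduled. The small downside is that some outcome data will be collected after discontinuation. Section 2.14 says enrolment has begun, so the amendment is most useful if made soon.

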### Statistical analysis

2.12

Sample size calculation was performed using PASS software (version 15.0, NCSS LLC). Based on preliminary data, the estimated mean (standard deviation) of the VAS numbness score after intervention for the treatment group (UA + WA) is 1.6 ± 1.0 cm, and for the control group (electroacupuncture) it is 2.41 ± 1.68 cm. To detect a between-group difference of 0.81 cm with 90% power (*β* = 0.10) and a two-sided *α* of 0.05, at least 41 participants are required in each group. Considering a 15% dropout rate, the final sample size is set at 48 participants per group (96 participants in total). This calculation complies with the CONSORT guidelines for randomized controlled trials.

All analyses will follow the intention-to-treat (ITT) principle, including all randomized participants. Additionally, for sensitivity analysis, a per-protocol set (PPS) analysis will be conducted, excluding participants with major protocol deviations (e.g., fewer than 8 acupuncture sessions, and use of prohibited medications). The primary outcome, the change in VAS numbness score over time points (baseline, 1 week, 4 weeks, 12 weeks, 24 weeks), will be assessed using a linear mixed-effects model (LMM). The model will include group, time, group-by-time interaction, and baseline VAS score as fixed effects. Random intercepts and slopes will account for within-individual variability. Missing data will be handled using multiple imputation (MI) with fully conditional specification (FCS) in SAS 9.4 (SAS Institute), generating 10 imputed datasets. Estimates will be combined according to Rubin’s rules. Sensitivity analysis will compare MI with the last observation carried forward (LOCF). For secondary outcomes with continuous variables (e.g., JOA, SF-36), the same LMM structure as the primary outcome will be used. For ordinal/categorical variables (e.g., TCM syndrome score), proportional odds logistic regression or generalized estimating equations (GEE) will be applied to longitudinal ordinal data. For binary outcomes (e.g., adverse events), comparisons between groups will be made using the chi-square test or Fisher’s exact test (for small sample sizes). Risk ratios (RR) and 95% confidence intervals (CI) will be reported.

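### The withdrawal and efficacy-inclusion rules in section 2.3.3 are not reconciled with the intention-to-treat analysis in section 2.12, so the primary efficacy population is not uniquely defined

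*Protocol article*

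**What the plan says.** Section 2.12 (Statistical analysis) is explicit: "All analyses will follow the intention-to-treat (ITT) principle, including all randomized participants". It handles missing values by multiple imputation with ten datasets. It adds a per-protocol analysis, labelled as sensitivity, that drops major deviators; fewer than 8 acupuncture sessions is one of its two examples.

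Section 2.3.3 (Withdrawal and termination criteria) works differently. Among the withdrawal criteria are (4) "Individuals with poor compliance", (5) "Individuals with incomplete data affecting efficacy and safety evaluation" and (7) "Individuals who have not completed more than 2/3 of the treatment course". A bracket on criterion (7) says that it takes in patients who withdrew or were lost to follow-up. The termination paragraph then ends: "Those who have completed more than half of the treatment regimen should be included in the efficacy statistics".

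Section 2.6 (Interventions) sets three sessions on consecutive days, then three a week for 4 weeks. It halts acupuncture if numbness disappears, with follow-up continuing.

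**The concern.** If all randomised patients are analysed, a rule that admits patients to the efficacy statistics by the share of treatment completed has nothing to do. It acquires meaning only if those at or below half are left out. Criteria (5) and (7) point the same way. Whether data are too incomplete, or whether a patient lost to follow-up completed enough of the course, can be judged only afterwards, so these criteria work more like analysis exclusions than like decisions to stop treatment. If criterion (5) were used in that way, it would remove patients for whom the imputation is planned.

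At stake is who enters the primary comparison. Exclusions based on compliance, completeness of data or sessions attended arise after randomisation. They can depend on treatment and on outcome, and they need not be alike in the two arms. Two analysts following this text in good faith could build different primary datasets.

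**Working it through.** The plan states neither a total number of sessions nor a number of patients affected, so there is no figure of its own to reproduce on this point.

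**Session cuts.** Section 2.6 gives 3 + 3 × 4 = 15 sessions.

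| Rule | Source | Arithmetic | Sessions needed |
|---|---|---|---|
| More than half: counted in efficacy | 2.3.3, last sentence | 15 / 2 = 7.5 | 8 or more |
| More than two thirds: not withdrawn | 2.3.3, criterion (7) | 15 × 2/3 = 10 | 11 or more |
| Per-protocol set | 2.12 | fewer than 8 excluded | 8 or more |
| Primary analysis | 2.12 | all randomised | none |

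The half rule and the per-protocol cut coincide at 8. The two-thirds rule differs, so patients with 8, 9 or 10 sessions are withdrawn under criterion (7), yet counted in efficacy by the closing sentence and eligible for the per-protocol set on sessions.

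If the 4-week intervention period in section 2.1 were taken to mean 12 sessions in all, the cuts would be 7, 9 and 8. The two 2.3.3 rules would still disagree, now for 7 or 8 sessions.

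**Early responders.** On the 15-session schedule, the cumulative count is 3 after the first block, then 6, 9, 12 and 15 at the end of each thrice-weekly week. A patient whose numbness is gone at 6 sessions, and whose acupuncture is halted under section 2.6, is below both 2.3.3 cuts. One who stops at 9 is below the two-thirds cut. Section 2.3.3 states no exception for them. Non-responders who give up could fall below the same cuts.

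**Illustrative size.** Inputs: experimental-arm mean 1.6 cm, control-arm mean 2.41 cm, target difference 0.81 cm, 15% dropout and 48 per group (sections 2.5 and 2.12). Assumptions not in the documents: the excluded share equals that 15% (0.15 × 48 = 7.2, about 7 patients), exclusion is in the experimental arm only, and the excluded patients' mean m lies between 0 and 3.0 cm.

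Mean of those kept = (1.6 - 0.15m) / 0.85.

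| m (cm) | Mean of those kept (cm) | Shift (cm) | Difference from 2.41 (cm) |
|---|---|---|---|
| 0 (numbness gone) | 1.6 / 0.85 = 1.88 | +0.28 | 0.53 |
| 1.6 (same as the arm) | 1.36 / 0.85 = 1.60 | 0 | 0.81 |
| 3.0 (poor responders) | 1.15 / 0.85 = 1.35 | -0.25 | 1.06 |

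Relative to the target, the two ends are 0.28 / 0.81 = 35% and 0.25 / 0.81 = 31%, in opposite directions.

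**The case against.** The strongest reply is that section 2.12 is the dedicated analysis section and already gives the right rule: all randomised, missing data imputed, session cut confined to a sensitivity set. Section 2.3.3 never says that only patients past halfway are counted. Its closing sentence can be read inclusively, as protecting the data of someone who stopped after the halfway mark. Nor does any criterion say that a withdrawn patient leaves the intention-to-treat set or that collected data are discarded; most of the list reads naturally as leaving treatment or the trial.

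Much of this stands. A reader might infer that the primary result will be a completers' comparison carrying an intention-to-treat label. The document does not support that, because it would require section 2.3.3 to override section 2.12, and nothing says that it does. Equally, nothing limits the closing sentence to the per-protocol set or says that withdrawn patients still count, so the conflict remains.

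The size is also open to challenge. A reader might infer that exclusion would flatter the experimental arm by about 30% of the target. That would need a 3.0 cm mean among the excluded, which the protocol does not give and which is 1.4 SD above 1.6 on its SD of 1.0. It would also need exclusion in one arm only, and it would ignore early responders. Similar exclusions among controls would offset some or all of the shift. The 15% need not match the patients these rules remove: dropouts past halfway are kept by the closing sentence, and compliance withdrawals may not be part of the 15%.

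**Conclusion.** The concern holds as an unresolved contradiction about who is in the primary analysis. Section 2.3.3, if followed, gives a post-randomisation exclusion that section 2.12 rules out, and section 2.3.3 disagrees with itself for patients with 8 to 10 of 15 sessions. That the remaining patients are excluded is implied, not stated.

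Neither the direction nor the size of any bias can be fixed from the document. The range of +0.28 to -0.25 cm is an illustration for 15% excluded from one arm, with both ends near the extreme. It shows that the choice of population could matter against a 0.81 cm target; it does not predict an effect. The session counts rest on reading section 2.6 as 15 sessions, but the disagreement within 2.3.3 survives a 12-session reading. Because section 2.14 reports that enrolment has begun, this should be settled before any outcome data are analysed.

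**What to change.** Reconcile sections 2.3.3, 2.6 and 2.12 by amendment:

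- Delete the closing more-than-half sentence of 2.3.3, or confine it expressly to the per-protocol set.
- State once, in 2.12, that the primary efficacy population is all randomised participants, and that meeting a 2.3.3 criterion removes neither the patient nor the data already collected.
- Use a single session threshold, for the per-protocol set only. State there how patients whose acupuncture was halted because numbness disappeared are classified.
- Keep collecting numbness VAS at every Table 1 visit after treatment ends, unless consent is withdrawn, and impute only what is truly missing.

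No change to any clinical stopping rule is proposed. The cost is a small amendment plus added follow-up effort for patients who stop treatment. That effort is more than a telephone call, since section 2.8.1 has patients mark a 10 cm line, so a way to capture the mark is needed.

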### Randomization, allocation concealment, and blinding

2.4

Eligible patients will be randomly assigned to two groups: the treatment group (receiving warm needle acupuncture combined with Western medicine) and the control group (receiving electro-acupuncture). The randomization will be performed using the CHISS software for block randomization. The size of each block is n. Once the randomization scheme is generated, it will be kept by a third party independent of this study. To ensure allocation concealment, we use sealed opaque envelopes. These envelopes are prepared by an independent member of the research team, and participants draw an envelope randomly upon enrollment in the study to determine their treatment group. Clinical researchers will obtain the specific treatment plan for each patient through designated channels (such as by phone). Assessors will not be informed of the participants’ specific group assignments throughout the follow-up period. All assessment work will be carried out by assessors independent of the treatment process. These assessors will receive rigorous training before the study begins to ensure their standardized understanding and application of the VAS score, thereby ensuring the consistency and accuracy of the assessments. Assessors will be strictly restricted from accessing participants’ treatment group information throughout the follow-up period to maintain assessor blinding. Blind statistical analysis will also be implemented during the data aggregation and analysis phase, with statisticians remaining unaware of the participants’ treatment allocations to ensure the objectivity of the statistical analysis results. In the event of serious adverse events, emergency medical situations, or requests from participants, the sealed envelope containing the blinding information will be opened by an independent third party, and the reasons, time, and personnel involved in the unblinding will be recorded in detail and reported to the relevant committee promptly. Medical decisions will be made based on the unblinding results, and participants will be allowed to withdraw from the trial if necessary.

